##### Peripheral reaching

For peripheral reaching, participants are required to gaze at the fixation cross throughout each trial. A trial begins by pressing and holding down the start box. When touched, the start box disappears and the fixation cross cycles between white and red (at a rate of 60 Hz) until the trial ends. After a short delay (250–750 ms) a target appears at one of nine locations. While maintaining fixation, participants make one smooth reaching movement to try to touch the target. The target remains on the screen until a touch is recorded at any location, and a short beep is played once the target disappears. The experimenter then records the validity of the trial; ‘y’—valid, ‘e’—participant moved their eyes away from fixation, ‘v’—void trial.

Invalid (‘e’ or ‘v’) trials are repeated until a valid trial is recorded. The block ends after a minimum of 27 valid trials (three per target location), or after 50 valid and ‘eye-movement’ trials.

#### ​Radial reaching tasks

##### Stimulus and Apparatus

An infrared motion-tracking camera (Optotrak Certus, Northern Digital) is used to track the reaching movement. Infrared-emitting diodes (IREDs) are taped to the tip of the right and left index fingers of each participant to track the reach in each hand. The Optotrak samples the IRED’s 3D position at 100 Hz throughout each 2000 ms trial. The task is controlled by custom software written in LabView (National Instruments) programming environment. The stimuli and apparatus reported here are specific to UoE. At the second site, UEA, motion tracking was performed by using a Qualisys system (Gothenburg, Sweden) and a slightly different set up was used. 14

Participants are seated with their head placed in a chin-rest in line with the middle of the display. Stimuli are back-projected via a mirror onto a screen (1000 mm wide × 750 mm deep) that lies flat in-front of the participant. A webcam is placed on the screen 50 cm directly in-front of the participant, as a fixation point. The live webcam image feeds into a separate laptop, allowing the experimenter to monitor gaze. A start button is aligned to the centre of the screen, positioned 10 cm in-front of the participant, 40 cm away from fixation (figure 2). Targets are white circles (diameter=1.60°, 13.96 mm) presented at four eccentric locations (11.4°, 22.6°, 33.4° and 43.6° away from centre) on each side (figure 2).

##### Calibration

**Figure 2 F2:**
[figure not shown]
Target positions for the radial reaching task shown here on both the right-hand and left-hand sides, at 11.4°, 22.6°, 33.4° and 43.6° from fixation. The start button is positioned at the bottom of the screen 40 cm away from central fixation. A webcam is placed at the point of central fixation (midpoint).

A calibration procedure is carried out before the reaching tasks to record the IRED position at the actual target location. A target is displayed at one target location and the participant is instructed to cover it completely with their reaching finger. Once the target is covered, the experimenter presses the start button and the finger location is recorded for 2000 ms. A beep plays after 2000 ms, indicating that the participant can move their hand away from the target position. Another target appears at the next location and the same procedure is repeated. Calibration is run using the ipsilateral hand for four targets on the left side and four on the right.

##### Free reaching

Participants initiate a trial by pressing and holding down the start button. As soon as they push the button down, participants may look around the screen for a target. After 250–750 ms a target appears, participants then look directly at the target and reach to touch the target in one smooth movement. Optotrak recording is initiated simultaneously with target appearance, and the target disappearance is simultaneous with the end of the recording after 2000 ms. When the target disappears a short beep (100 ms, 440 Hz) plays, the participant leaves their finger at its landing position until they hear the beep. After the trial, the experimenter codes the trial validity with a key-press; ‘Return’—valid, ‘F1’—no eye-movement, ‘Esc’—void trial. If an invalid trial (‘F1’ or ‘Esc’) is coded the trial gets recycled to the end of the block.

The block ends once 28 valid trials (7 per target location) are recorded, or after 50 valid and ‘no eye-movement’ trials.

##### ​Peripheral reaching

To assess reaching accuracy in the periphery participants are required to look directly at central fixation (the webcam) throughout each trial. Participants initiate a trial by pressing and holding down the start button. After 250–750 ms a target appears. While maintaining gaze on the webcam participants make one smooth reaching movement to try to touch the target. After the reach, participants leave their finger at its landing position until a short beep (100 ms, 440 Hz). The target remains on screen for 2000 ms after the trial begins. The motion-tracker records the reach throughout the 2000 ms trial. At the end of the trial, the experimenter codes trial validity; ‘Return’—valid trial, ‘F1’—eye movement during trial, ‘Esc’—void trial. If an invalid trial (‘F1, ‘Esc’) is recorded then the trial is recycled to the end of the block.

The block ends after 28 valid trials (7 per target location) are recorded, or after 50 valid and ‘eye-movement’ trials.

## Analysis plan

### ​Lateral reaching task

For the critical analyses, a single measure of reaching accuracy is taken for each participant, for each combination of viewing condition (free, peripheral) and side (non-dominant, dominant). For each response, the absolute error (in mm, x-axis and y-axis) is recorded as the distance of the reach endpoint from the target midpoint. The median absolute error is then calculated for each target eccentricity, across responses to the three targets at that eccentricity, for each combination of viewing condition and side. The average absolute error is then calculated as the mean of the medians for the three eccentricities, to give the single measure of reaching accuracy for each viewing condition at each side.

For the comparison of individual patients against control performance, the data are further compressed to a single index of performance per side, by subtracting reaching accuracy in the free vision condition from that in the peripheral condition. We call this value the Peripheral Misreaching Index (PMI).

#### Analysis of single-case deficits

We will screen the control group for outliers that might suggest abnormalities, as such values would reduce the (already low, see figure 3) power to detect single-case deficits. We will use a robust method of outlier detection based on the median absolute deviation (MAD). The MAD can be multiplied by the consistency constant 1.4826 to estimate the SD, assuming a normal distribution. Each control participant’s PMI can be expressed as a modified Z-score (Z′) by subtracting the group median, divided by the MAD *1.4826. If Z′ exceeds 2.5 on either side, that participant will be excluded, and replaced. Our simulations suggest that, for a group size of 24, we would expect to exclude (on average)<1 participant (~0.67) by this criterion.

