**Figure 3 F3:**
[figure not shown]
Relation between(A) control sample size and power to detect a single-case deficit in a one-tailed test, for different sizes of deficit (D, expressed as SD of control mean). (B) D and power to detect a deficit, given a control sample size of 24, for adjusted (.025) and unadjusted (.05) alpha criteria.

We will next assess, for each side, whether the PMI of controls is related to age or sex, by computing Pearson’s correlations. If the correlation is ≥0.3 on either side, then that variable will be included as a covariate in the subsequent case–control comparisons for both sides.

Case–control comparisons will then be run to compare each patient’s PMI against control performance on each side of space. These comparisons will be based on Crawford and Howell's^15^ modified t-test; or, if covariates are included, we will use the Bayesian Test of Deficit with covariates.^16^ The individual tests will be one-tailed, with an alpha level set to 0.025, in order to constrain per-patient alpha level (across the two sides) to 0.05. If a patient shows a deficit on either side that meets the adjusted criterion (0.025), they will be classified as showing periperheral misreaching. If a patient shows a deficit on either side that would meet the unadjusted criterion (0.05), but not the adjusted criterion, they will be classified as showing borderline peripheral misreaching.

Finally, a binomial test will test whether the rate of observed peripheral misreaching exceeds the rate expected by chance (ie, the per-patient adjusted alpha level of 0.05). A significant outcome (p<0.05) for either patient group will indicate that peripheral misreaching is a feature of this patient group. The observed rate of peripheral misreaching will provide an estimate of how common it is. We will run a further analysis including borderline cases and compare the rate of peripheral misreaching in each patient group against the appropriate chance level of 0.10.

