### Power considerations

The target sample sizes (N=24 per group) are based on power considerations related to the main inferential analyses, the case–control comparisons and binomial tests of rates of peripheral misreaching deficits for the lateral reaching task.

The control sample size of 24 will provide close to the maximum power for case–control tests of deficit (figure 3A). Note that high power for these comparisons is inherently unachievable unless the deficit being tested for is very large. We do not know how large any misreaching deficits may be in our patient groups, but our control sample size will provide close to the maximum achievable power to detect them if they exist. Figure 3B illustrates more fully the relationship between deficit size (D) and power, for the adjusted alpha level (0.025) and unadjusted alpha level (0.05) by which we will determine peripheral misreaching deficits and borderline cases, respectively (Analysis of single case deficits section).

The main hypothesis is that peripheral misreaching will be found in a significant proportion of patients with AD and MCI. For one-sample binomial test to determine whether the observed rate of peripheral misreaching exceeds the chance level of 0.05, a sample size of 24 has >0.9 power. Provided that the true population proportion is at least 0.2 (1 in 5). This is appropriate to our aims, since peripheral misreaching would be of limited significance in these clinical populations if its prevalence were less than 1 in 5.

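### Controls with high PMI are screened out but patients are not, so the fixed 0.05 and 0.10 chance rates are too low and the false group claim rate roughly doubles

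*Protocol article*

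**What the plan says.** Under *Analysis of single-case deficits* the protocol article announces: "We will screen the control group for outliers that might suggest abnormalities". The reason given is that such values would reduce a power that is already low. Each control's PMI is centred on the group median and scaled by the MAD: "The MAD can be multiplied by the consistency constant 1.4826 to estimate the SD, assuming a normal distribution". If the resulting Z′ "exceeds 2.5 on either side, that participant will be excluded, and replaced". The expected effect is stated: for 24 controls, "we would expect to exclude (on average)<1 participant (~0.67) by this criterion". No screen is described for patients.

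The same section then compares each patient with these controls by the modified t-test (or its Bayesian counterpart if covariates enter): "The individual tests will be one-tailed, with an alpha level set to 0.025". A deficit on either side classifies the patient as misreaching. For each patient group, a binomial test compares the observed rate with "the per-patient adjusted alpha level of 0.05". A significant result for either group is read as showing that misreaching characterises that group. A further analysis adds borderline cases and uses 0.10. *Power considerations* names these comparisons and binomial tests for lateral reaching as the main inferential analyses. The radial task follows the same plan.

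**The concern.** The modified t-test has a false-positive rate of 0.025 per side only if the controls and a patient without a deficit come from the same population. The screen cuts the upper tail of the control sample, which is the tail on which patients are judged. It lowers both the control mean and the control SD, so an unaffected patient crosses the cut-off too often. Neither the cut-off nor the chance rate allows for this.

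The main conclusion rests on exceeding 0.05. If the real chance rate is higher, the test can be significant in a group with no deficit. The observed rate, which the plan also uses to estimate how common misreaching is, is biased upward too.

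**Working it through.** **Inputs from the protocol article.** 24 controls and 24 patients per patient group; Z′ > 2.5 on either side, scale 1.4826 × MAD; one-tailed alpha 0.025 per side; classification on either side; chance rates 0.05 and 0.10; binomial p < 0.05.

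**Assumptions not in the document.** Normal PMI, no true deficit, between-side correlation 0 to 0.8, and the replacement procedure: one pass (replacements not re-screened) or repeated until no control is flagged.

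**1. The plan's own figure.** In simulated samples of 24 healthy normal controls, the mean number with Z′ > 2.5 on either side is 0.672, 0.658, 0.637 and 0.58 at correlations 0, 0.3, 0.5 and 0.8. The stated ~0.67 therefore reproduces from controls with nothing wrong with them. Reading the rule as |Z′| > 2.5 on either side gives about 1.3 for correlations 0 to 0.5, so the upper-tail reading fits the text.

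**2. Nominal operating characteristics.** The single-case cut-off is t(0.975; 23 df) × √(25/24) = 2.069 × 1.0206 = 2.11 control SDs above the control mean. With independent sides the per-patient rate is 1 − 0.975² = 0.049. The exact binomial test against 0.05 rejects at 4 or more of 24: P(≥4) = 0.0298, while P(≥3) = 0.116.

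**3. With the screen.** Each of 20,000 simulated trials per row draws, screens and replaces controls, then tests 24 unaffected patients. The Monte Carlo standard error at 0.11 is √(0.11 × 0.89 / 20,000) = 0.002.

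| Side correlation | Screen | Mean control SD (true 1) | Per-patient false positive | P(≥4 of 24), one group | In at least one of two groups |
|---|---|---|---|---|---|
| 0 | none | 0.99 | 0.049 | 0.053 | 0.096 |
| 0 | one pass | 0.95 | 0.065 | 0.114 | 0.186 |
| 0 | re-screened | 0.95 | 0.073 | 0.139 | 0.216 |
| 0.3 | none | 0.99 | 0.048 | 0.056 | 0.099 |
| 0.3 | one pass | 0.95 | 0.064 | 0.112 | 0.182 |
| 0.3 | re-screened | 0.94 | 0.073 | 0.140 | 0.214 |
| 0.5 | none | 0.99 | 0.045 | 0.050 | 0.088 |
| 0.5 | one pass | 0.95 | 0.062 | 0.110 | 0.178 |
| 0.5 | re-screened | 0.94 | 0.070 | 0.136 | 0.210 |
| 0.8 | none | 0.99 | 0.040 | 0.041 | 0.071 |
| 0.8 | one pass | 0.95 | 0.055 | 0.088 | 0.144 |
| 0.8 | re-screened | 0.93 | 0.063 | 0.123 | 0.186 |

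As a check on the first one-pass row, the simulated per-test rate is 0.0333, and 1 − (1 − 0.0333)² = 0.0655, against 0.065 in the table.

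**4. What the screen itself contributes.** The rise from 0.030 to 0.041-0.056 occurs without any screen: all patients share one control sample, so their classifications are not independent. The screen then multiplies the unscreened rate by about 2 with one pass (0.112/0.056 = 2.0; 0.110/0.050 = 2.2) and by 2.5 to 3 with re-screening (0.140/0.056 = 2.5; 0.123/0.041 = 3.0).

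**5. Borderline analysis (chance rate 0.10, rejects at 6 or more of 24, nominal 0.028).** Per-patient rates are 0.097-0.120 with one pass and 0.107-0.128 re-screened. False claims are 0.078-0.115 and 0.106-0.141, against 0.034-0.057 unscreened.

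**6. Critical count.** With one pass, 5 of 24 has size of about 0.04-0.05 (0.054 for independent sides). With re-screening, 5 of 24 reaches about 0.08 and 6 of 24 about 0.04. Entering a higher chance rate in an ordinary binomial test is not enough. At 0.065, P(≥4) = 1 − (0.199 + 0.333 + 0.266 + 0.136) = 0.067, but the simulated value is 0.114, because the binomial ignores the shared controls.

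**The case against.** The strongest counter-argument is that the rule does a real job. Controls are eligible on the absence of *reported* neurological conditions, so an undetected abnormal control is plausible. If one control is shifted by 4 SD on both sides (an assumption), detection of a 2.5 SD patient deficit falls from about 0.83 with the screen to about 0.53 without it, and the unscreened test becomes very conservative. The rule is also pre-specified, robust and disclosed with its expected exclusion count. This stands as a reason not to make the unscreened controls the primary reference. It does not restore the error rate, because pre-specification removes discretion and leaves the bias in place.

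Several stronger readings are tempting and are not supported:

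- *The rule removes a healthy control two times in three.* The 0.67 is a mean count. At least one exclusion occurs in about 40-43% of all-normal samples; in the rest the analysis is identical to the unscreened one. Control data are already collected (*Study setting*), so whether anyone is flagged can already be known.
- *The screen takes the error from 3% to 14%.* The unscreened baseline is 4-5.6%, and 14% needs re-screening, which the text does not state.
- *The error is far larger because PMI is skewed.* A right-skewed lognormal with re-screening gives about 65%, but 19% arises there without any screen, and the document says nothing about the shape of PMI.

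The group-level ANOVA of severity complements the binomial test but does not correct its size.

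**Conclusion.** The point holds: as written, 0.05 and 0.10 are not the chance rates of the procedure described. For the main test the per-patient rate is about 0.055-0.065 with one-pass replacement and 0.063-0.073 with re-screening. The probability of a false claim per patient group is about 9-11% and 12-14% respectively, against 4-5.6% unscreened and 3% nominal. For the borderline rate the excess is smaller and disappears in one setting (0.097 at correlation 0.8, one pass), although false claims there still exceed 5%.

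These figures assume normal PMI, side correlations of 0 to 0.8, 24 complete datasets per group and the modified t-test. The covariate branch and the radial task, with its site-specific control groups, were not simulated.

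**What to change.** Keep the screen if it is wanted, and calibrate the test to it. Replace the 0.05 and 0.10 chance rates and the binomial critical counts by values from a simulation that includes the screening and replacement step, the shared control sample and the observed between-side correlation. For the main test this gives about 5 of 24 with one-pass replacement, or 6 of 24 with re-screening, instead of 4. State whether replacements are re-screened. Report the analysis on all eligible controls as a sensitivity analysis. Repeat the calibration for the radial task with its same-site control numbers.

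The work is computing and wording: control data were already collected and 8 of 48 patients had taken part when the article was written. The statistical cost is a stricter threshold and so lower power of the binomial test. If the proportion of patients classified is 0.2, the exact binomial probability of reaching the threshold is 0.736 at 4 of 24 and 0.540 at 5 of 24. Part of the power at 4 of 24 was bought by the inflated error rate.

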**Figure 3 F3:**
[figure not shown]
Relation between(A) control sample size and power to detect a single-case deficit in a one-tailed test, for different sizes of deficit (D, expressed as SD of control mean). (B) D and power to detect a deficit, given a control sample size of 24, for adjusted (.025) and unadjusted (.05) alpha criteria.

We will next assess, for each side, whether the PMI of controls is related to age or sex, by computing Pearson’s correlations. If the correlation is ≥0.3 on either side, then that variable will be included as a covariate in the subsequent case–control comparisons for both sides.

Case–control comparisons will then be run to compare each patient’s PMI against control performance on each side of space. These comparisons will be based on Crawford and Howell's^15^ modified t-test; or, if covariates are included, we will use the Bayesian Test of Deficit with covariates.^16^ The individual tests will be one-tailed, with an alpha level set to 0.025, in order to constrain per-patient alpha level (across the two sides) to 0.05. If a patient shows a deficit on either side that meets the adjusted criterion (0.025), they will be classified as showing periperheral misreaching. If a patient shows a deficit on either side that would meet the unadjusted criterion (0.05), but not the adjusted criterion, they will be classified as showing borderline peripheral misreaching.

Finally, a binomial test will test whether the rate of observed peripheral misreaching exceeds the rate expected by chance (ie, the per-patient adjusted alpha level of 0.05). A significant outcome (p<0.05) for either patient group will indicate that peripheral misreaching is a feature of this patient group. The observed rate of peripheral misreaching will provide an estimate of how common it is. We will run a further analysis including borderline cases and compare the rate of peripheral misreaching in each patient group against the appropriate chance level of 0.10.

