**Ethics and dissemination:**

Ethical approval was provided by the National Health Service (NHS) East of England, Cambridge Central Research Ethics Committee (REC 19/EE/0170). The results of this study will be published in a peer-reviewed journal and presented at academic conferences.

Strengths and limitations of this studyThe first study to systematically assess visually guided reaching in patients with cognitive impairment.Includes a simple tablet-based task (lateral reaching) that could be readily translated to clinical settings to assess the presence of peripheral misreaching.Case–control statistical tests of deficit are inherently low powered, so subtle deficits of reaching may not be detected at the level of individual patients.

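### The proportion of patients flagged is treated as the prevalence of misreaching, and the claimed power above 0.9 at 1 in 5 is not met on either reading of 0.20

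*Protocol article*

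**What the plan says.** Under Analysis of single-case deficits, each patient's Peripheral Misreaching Index is compared with controls on each side, one-tailed at 0.025. A patient significant on either side is classified as misreaching. A binomial test then asks whether the rate "exceeds the rate expected by chance (ie, the per-patient adjusted alpha level of 0.05"), and "A significant outcome (p<0.05) for either patient group will indicate that peripheral misreaching is a feature of this patient group". The same paragraph adds: "The observed rate of peripheral misreaching will provide an estimate of how common it is".

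Under Power considerations, "The target sample sizes (N=24 per group) are based on power considerations related to the main inferential analyses", namely the case–control comparisons and the binomial tests for the lateral task. The binomial claim is that "a sample size of 24 has >0.9 power", with the condition "Provided that the true population proportion is at least 0.2 (1 in 5"). The choice of 0.2 is defended on the ground that "peripheral misreaching would be of limited significance in these clinical populations if its prevalence were less than 1 in 5".

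The article is open about the weakness of the single-case test. The strengths and limitations list says these tests have low power, "so subtle deficits of reaching may not be detected at the level of individual patients". Power considerations says that high power is out of reach unless the deficit is very large, and that the size of the deficit in patients is unknown.

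**The concern.** Two quantities carry one name. The binomial test and its power concern the rate at which patients are flagged. The 1-in-5 justification and the statement about how common misreaching is concern the proportion of patients who have the deficit. They coincide only when missed cases and false positives happen to cancel. The article states that affected patients can be missed and sets the false-positive rate, but carries neither into the estimate of frequency or into the link between 1 in 5 and power.

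This affects the analyses on which the sample size rests. A published figure for how common misreaching is could be well below the true frequency if deficits are moderate, and would be expected at about 0.04–0.05 if no patient were affected. Readers would also believe that the study is better able to detect a prevalence of 1 in 5 than it is.

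**Working it through.** **Inputs from the article:** 24 patients per group; 24 controls; chance rate 0.05; binomial significance level 0.05; alternative 0.20; single-case tests one-tailed at 0.025 per side, either side counting.

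**Assumed, because the article does not give them:** deficit size D of 2, 3 or 4 control SDs; between-side correlation of 0, 0.5 or 0.8; deficit on one side or on both. Control outlier screening and covariates are ignored. Flags are treated as independent across patients, as the binomial test does.

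**1. The stated power, with 0.20 read as the flagged rate.** The rule is the smallest r with P(X ≥ r) ≤ 0.05 for X ~ Binomial(24, 0.05).
- r = 3: alpha 0.116, too large. Its power at 0.20 would be 0.886, still below 0.9.
- r = 4: alpha 0.030. Power = P(X ≥ 4) for Binomial(24, 0.20) = 0.736.

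So the figure above 0.9 is not reproduced. A normal approximation with the correct variances gives 0.83 one-sided and 0.78 two-sided. Values above 0.9 appear only if the null variance is also used under the alternative (0.96 one-sided, 0.92 two-sided) or if both patient groups are pooled (n = 48, r = 6: 0.938). Neither is an exact test per group. With 24 patients, power 0.9 needs a flagged rate of about 0.26. At a flagged rate of 0.20, power 0.9 is first reached with 38 patients.

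**2. Single-case sensitivity on one side.** Noncentral t, df = 23, noncentrality D/√(1 + 1/24), one-tailed 0.025: D = 1, 0.15; D = 2, 0.47; D = 2.5, 0.65; D = 3, 0.80; D = 4, 0.96.

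**3. The flagging rule.** Because either side counts, sensitivity (Se) and the per-patient false-positive rate (FP) were simulated for the two-sided rule. FP was about 0.049, 0.046 and 0.039 at correlations 0, 0.5 and 0.8.

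**4. From prevalence to power.** Flagged rate q = prevalence × Se + (1 − prevalence) × FP. Power = P(X ≥ 4) for Binomial(24, q). At prevalence 0.20:

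| D | Either-side Se | q | Power |
|---|---|---|---|
| 2 | 0.47–0.72 | 0.12–0.18 | 0.35–0.66 |
| 3 | 0.80–0.96 | 0.19–0.23 | 0.70–0.84 |
| 4 | 0.96–1.00 | 0.22–0.24 | 0.82–0.86 |

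Each range runs from a one-sided deficit with correlation 0.8 to a bilateral deficit with correlation 0. The ceiling, with Se = 1 and FP = 0.05, is q = 0.20 + 0.80 × 0.05 = 0.24, power 0.86.

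**5. Bias of the flagged rate as an estimate of prevalence.**
- Nobody affected: expected rate 0.04–0.05.
- Prevalence 0.20, FP 0.05: q = 0.20 only when Se = 0.80 (0.16 + 0.04). Lower Se understates prevalence; higher Se overstates it, up to 0.24.
- Prevalence 0.40, D = 2: lowest 0.40 × 0.47 + 0.60 × 0.04 = 0.21; highest 0.40 × 0.72 + 0.60 × 0.05 = 0.32.

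**The case against.** The strongest defence is operational. The article defines misreaching as a significantly abnormal index on either side. On that definition the flagged proportion is the natural estimate, and the population proportion in the power statement can mean the proportion classified. The split into affected patients with a fixed D and unaffected patients is not in the article. This has force, but it does not fit the defence of 0.2 as a prevalence that matters in clinical populations, and it does not rescue the power: on that reading the exact figure is 0.74.

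Three stronger readings are tempting and are not supported.
- A reader might infer that single-case sensitivity is simply poor. That holds up to about D = 2 to 2.5. At D = 3 the flagged rate is 0.19–0.23 for a prevalence of 0.20, nearly unbiased, and the article says that D is unknown.
- A reader might infer that the plan ignores false positives. It does not: 0.05 is the null of the test, and 0.10 is the null when borderline cases are included. They are left out only of the estimate and of the prevalence argument.
- A reader might infer that the plan will take a non-significant result as evidence of prevalence below 1 in 5. It interprets only a significant result.

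Nor is low sensitivity the only cause of the power shortfall, since the figure already fails with 0.20 taken literally as the flagged rate. The borderline analysis and the group-level ANOVA give some cover for common, moderate deficits, but neither estimates prevalence, and the sample size is not based on them.

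**Conclusion.** The point holds in this form. The article equates the flagged rate with prevalence, and its power above 0.9 is wrong on either reading: 0.74 if 0.20 is the flagged rate, and at most 0.86 if 0.20 is the prevalence, falling to 0.35–0.66 for a 2-SD deficit. The 0.74 needs only the article's own inputs and an exact test. The prevalence-based figures rest on the assumed D, between-side correlation and laterality. The direction of bias in the frequency estimate depends on sensitivity: downward for moderate deficits, slightly upward for very large ones or when few patients are affected. The flaw lies in the stated power and in how the result is labelled; the test against chance is not invalidated by it.

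**What to change.** In Power considerations, replace the figure above 0.9 with 0.74 for a true flagged rate of 0.20, and say that 0.20 is a flagged rate. Add a small table of power by prevalence and D, computed from either-side sensitivity.

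In Analysis of single-case deficits, report the result as the proportion classified as abnormal, with an exact 95% CI, and state that it is not an estimate of prevalence.

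If an implied prevalence is wanted, give it only as a sensitivity range over D: (observed rate − FP)/(Se − FP), truncated at 0 and 1, with either-side Se and the per-patient FP. Figure 3B should not supply Se, because by its caption it shows the power of a single test at each alpha. For example, with an observed rate of 0.16, FP 0.05 and a bilateral 2-SD deficit at correlation 0.5, the single-test value gives 0.11/(0.467 − 0.05) = 0.26, while the either-side value gives 0.11/(0.64 − 0.05) = 0.19.

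The cost is a less favourable stated power, one small table and some rewording.
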